## Abstract

**Background:**

Adding cyclic short sustained inflations (sigh) to assisted ventilation yields optimizes lung recruitment, decreases heterogeneity and reduces inspiratory effort in patients with acute hypoxemic respiratory failure (AHRF). These findings suggest that adding sigh to pressure support ventilation (PSV) might decrease the risk of lung injury, shorten weaning and improve clinical outcomes. Thus, we conceived a pilot trial to test the feasibility of adding sigh to PSV (the PROTECTION study).

**Methods:**

PROTECTION is an international randomized controlled trial that will be conducted in 23 intensive care units (ICUs). Patients with AHRF who have been intubated from 24 h to 7 days and undergoing PSV from 4 to 24 h will be enrolled. All patients will first undergo a 30-min sigh test by adding sigh to clinical PSV for 30 min to identify early oxygenation responders. Then, patients will be randomized to PSV or PSV + sigh until extubation, ICU discharge, death or day 28. Sigh will be delivered as a 3-s pressure control breath delivered once per minute at 30 cmH_2_O. Standardized protocols will guide ventilation settings, switch back to controlled ventilation, use of rescue treatments, performance of spontaneous breathing trial, extubation and reintubation. The primary endpoint of the study will be to verify the feasibility of PSV + sigh evaluated through reduction of failure to remain on assisted ventilation during the first 28 days in the PSV + sigh group versus standard PSV (15 vs. 22%). Failure will be defined by switch back to controlled ventilation for more than 24 h or use of rescue treatments or reintubation within 48 h from elective extubation. Setting the power to 80% and first-risk order to 5%, the computed size of the trial is 129 patients per arm.

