**Discussion:**

PROTECTION is a pilot randomized controlled trial testing the feasibility of adding sigh to PSV. If positive, it will provide physicians with an effective addition to standard PSV for lung protection, able to reduce failure of assisted ventilation. PROTECTION will provide the basis for a future larger trial aimed at verifying the impact of PSV + sigh on 28-day survival and ventilator-free days.

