As prospective clinical trials including long-term use of sigh during assisted ventilation have not been performed yet, we conceived a pilot randomized controlled trial (RCT) to verify the clinical feasibility of the addition of sigh to PSV (PSV + sigh) in comparison to standard PSV. Therefore, the objective of the present trial is to determine whether ventilation by PSV + sigh can be applied early and safely in intubated patients with AHRF and successfully maintained until extubation. Specifically, the primary endpoint is to evaluate whether PSV + sigh, as compared to PSV, is associated with reduced failure of assisted ventilation, with failure defined as (1) prolonged switch to controlled ventilation; (2) use of rescue therapies for refractory hypoxia or (3) early need for reintubation after elective extubation.

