### Sample size

The sample size was computed based on the hypothesis that PSV + sigh might decrease the rate of failure of assisted ventilation compared to standard PSV. Based on previous data [21], the expected proportion of failure in patients undergoing PSV will be 22% and we hypothesized a proportion of 15% for patients in the PSV + sigh group. Assuming non-inferiority of PSV + sigh treatment, with a tolerance of 5% we estimated that a sample size of 258 patients (with 129 patients per study arm) will be sufficient to assess feasibility of the PSV + sigh strategy in this pilot phase with power of 0.8 and alpha 0.05.

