### Statistical analysis

Continuous normally distributed variables will be expressed by their mean and standard deviation or as medians and their interquartile ranges when not normally distributed. Categorical variables will be expressed as number and proportion (%). To assess the feasibility of PSV + sigh as compared to PSV (i.e., the primary endpoint), we will compute the proportion of patients experiencing at least one of the following events in each arm: switch to controlled ventilation for ≥ 24 h consecutively; use of PEEP ≥ 15 cmH2O, prone positioning, inhaled nitric oxide, extracorporeal membrane oxygenation or reintubation within 48 h from extubation.

We will compare the two proportions using the one-tailed non-inferiority test for proportions with a 5% tolerance. We will use 0.05 as the significance level. The same method will be adopted to evaluate the safety of PSV + sigh, which is a secondary endpoint. Prevalence of sigh responders in the two arms will be compared using the chi-squared or Fisher’s exact test. Ventilator-free days will be calculated as the difference between the duration of follow up (up to 28 days) and the number of days of intubation before successful extubation or separation from mechanical ventilation for tracheostomized patients. For all the secondary endpoints, we will use the chi-squared or Fisher’s exact test in the case of binary variables or the *t* test or Wilcoxon signed rank test for continuous variables. Time to death or extubation will be analyzed using Kaplan-Meier survival curves. Adjustement for potential confounding factors will be evaluated using appropriated regression models.

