Key determinants of VILI in patients with AHRF undergoing assisted ventilation include elevated ventilation pressures and inspired fraction of O_2_ (FiO_2_) [25]; heterogeneous distribution of alveolar collapse that increases the regional tidal volume/end expiratory lung volume (Vt/EELV) ratio (i.e., the regional lung strain) [8] and strenuous inspiratory effort and low regional compliance that determines elevated regional transpulmonary pressure (i.e., the regional lung stress) [10]. To this end, previous studies showed that the addition of sigh to assisted mechanical ventilation improves oxygenation without increasing ventilation pressures and FiO_2_; decreases the tidal volumes by decreasing the patient’s inspiratory drive; increases the EELV by regional alveolar recruitment; decreases regional heterogeneity of lung parenchyma; decreases patients’ inspiratory efforts limiting transpulmonary pressure and improves regional compliance [11–16, 26]. Of note, the improvement in gas exchange and lung mechanics disappears after sigh discontinuation [12]. In conceiving this study, we reasoned that long-term application of sigh during PSV might decrease the risk of VILI through various synergic mechanisms, possibly decreasing the duration of mechanical ventilation and mortality in patients with AHRF. To date, no RCT has tested the long-term safety and feasibility of the application of sigh. Therefore, before testing the effects of sigh on clinical outcome in a RCT, the feasibility of long-term use of sigh had to be investigated: this is the primary aim of the PROTECTION trial. Moreover, data on the safety of sigh will be collected, evaluating potential adverse effects including development of pneumothorax or other signs of barotrauma and hemodynamic instability. Finally, the sample size was calculated based on a potential deacrese in failure to remain on assisted ventilation from 22% during PSV to 15% during PSV + sigh, so that the potential to promote spontaneous breathing by addition of sigh will already be tested.

We anticipate the PROTECTION trial to be highly feasible, as study procedures are mainly limited to ventilation settings and do not include complex interventions, with limited burden on daily activities. PSV + sigh is an easy-to-implement ventilation mode and, for the present study, we will use high-performance ICU ventilators already available in each clinical unit, dramatically decreasing the study costs.

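### The abstract attaches 80% power and 129 per arm to a reduction in failure (22% to 15%), but that size gives 80% power only for the planned non-inferiority test; power to show a reduction is about 30% to 42%

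*Protocol article*

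**What the plan says.** Two descriptions of the primary comparison stand in the protocol article.

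**A reduction in failure.**
- Abstract, Methods: feasibility is judged through "reduction of failure to remain on assisted ventilation during the first 28 days in the PSV + sigh group versus standard PSV (15 vs. 22" (percent). The sizing statement follows shortly after: "Setting the power to 80% and first-risk order to 5%, the computed size of the trial is 129 patients per arm". No margin is given.
- Background, last paragraph: "the primary endpoint is to evaluate whether PSV + sigh, as compared to PSV, is associated with reduced failure of assisted ventilation".
- Main Discussion: the size is said to rest on the fall from 22% to 15%, "so that the potential to promote spontaneous breathing by addition of sigh will already be tested".
- Abstract, Discussion: if the trial is positive, "it will provide physicians with an effective addition to standard PSV for lung protection, able to reduce failure of assisted ventilation".

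**Non-inferiority.**
- Sample size: this section opens with the hypothesis that sigh might lower failure and gives the control rate ("the expected proportion of failure in patients undergoing PSV will be 22" percent) and 15% for the sigh arm. It then sizes the trial thus: "Assuming non-inferiority of PSV + sigh treatment, with a tolerance of 5" percent, with power 0.8 and alpha 0.05, giving 258 patients.
- Statistical analysis: "We will compare the two proportions using the one-tailed non-inferiority test for proportions with a 5% tolerance", at a significance level of 0.05.

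**The concern.** Showing that failure is reduced and showing that it is not more than 5 points higher are different claims, and they need very different numbers of patients. The abstract quotes a power for the first that belongs to the second. A reader who sees only the abstract would take the trial to have an 80% chance of demonstrating a 7-point reduction if one exists.

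Interpretation is at stake on both sides. If non-inferiority is met, the abstract has already written an efficacy conclusion that the test does not support. If no reduction is shown, readers may take that as the negative result of an adequately powered superiority trial, when the chance of showing the reduction was below one half from the start.

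**Working it through.** **Inputs.** Failure 22% (PSV) and 15% (PSV + sigh), tolerance 5 points, power 0.80, alpha 0.05 and 129 per arm, from Sample size; one-tailed test at 0.05, from Statistical analysis; 1:1 allocation, from Randomization.

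**1. Reproduce the planned size (non-inferiority, one-sided 5%).**

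n per arm = (z₀.₉₅ + z₀.₈₀)² × [p₁(1−p₁) + p₂(1−p₂)] / (benefit + margin)²

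= (1.645 + 0.842)² × (0.22×0.78 + 0.15×0.85) / (0.07 + 0.05)²

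= 6.183 × 0.2991 / 0.0144 = 128.4, so **129 per arm**.

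The plan's figure is reproduced. The distance being tested is 12 points: the assumed 7-point benefit plus the 5-point margin. Power at 129 is 80.2% by the normal approximation and 80.5% by exact enumeration of the Wald rule. Other readings do not give 129: non-inferiority at one-sided 0.025 needs 164, and superiority needs 380 (one-sided 5%) or 482 (two-sided 5%).

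**2. Power at 129 per arm to show the reduction itself.** The distance is now 7 points.

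SE = √(0.2991/129) = 0.0482

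- Two-sided 5%: 0.07/0.0482 − 1.96 = −0.51, power 31% (30.4% with the pooled variance under the null; 30.2% by exact enumeration of the chi-squared test).
- One-sided 5%: 0.07/0.0482 − 1.645 = −0.19, power 42% (42.2% pooled; 42.6% exact).
- Fisher's exact test is lower: 25.3% two-sided, 35.9% one-sided.

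**3. Size needed for 80% power to show the reduction.** 482 per arm two-sided or 380 one-sided, without continuity correction. Against 129, that is 482/129 = 3.7 times or 380/129 = 2.9 times the planned size.

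**4. What a positive primary result can look like.** Take 28/129 failures on PSV (21.7%) and 23/129 on PSV + sigh (17.8%).

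- Difference −3.9 points; SE = √[(0.217×0.783 + 0.178×0.822)/129] = 0.0495.
- One-sided 95% upper limit: −3.88 + 1.645×4.95 = +4.3 points. This is below 5, so non-inferiority is declared.
- Two-sided 95% interval: −3.88 ± 1.96×4.95, that is −13.6 to +5.8 points. This includes an increase in failure.

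With 28 control failures, a significant reduction by the pooled test would need 17 or fewer sigh failures (one-sided) or 16 or fewer (two-sided). Sigh counts of 18 to 23 would therefore meet the primary criterion without showing a reduction at either level.

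**5. How often this would happen.** If 22% and 15% are the true rates, the chance of meeting non-inferiority without a significant reduction is 80.5 − 42.6 = 38% (one-sided) or 80.5 − 30.2 = 50% (two-sided).

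**The case against.** The strongest reply is that the operative text is clear. Sample size and Statistical analysis agree on one primary test, one margin and one level, and a statistician following them would run the right analysis on the right number of patients. The trial is called a pilot of feasibility, the Background first frames the objective as early, safe and sustained use, and survival and ventilator-free days are left to a larger trial. Assuming a benefit when sizing a non-inferiority comparison is legitimate, and the assumed 15% is stated openly.

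Much of this stands, and it limits the point in four ways.

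- A reader might infer that the sample size is miscalculated. It is not; it reproduces.
- A reader might infer that every place with the reduction wording also claims 80% power for it. Only the Methods part of the abstract does. The Background has no figures, the main Discussion gives the two rates without the power, and the abstract's Discussion gives no numbers.
- A reader might infer that superiority will never be tested. The article describes no superiority test of the primary composite, but the analysis plan is not shown and may contain one. The article does plan between-group tests of secondary endpoints, including use of rescue treatments.
- A reader might count as an error that power is only about 25% if both arms truly fail at 22% (0.05/√(2×0.22×0.78/129) − 1.645 = −0.68). That is useful context for a design that relies on a 7-point benefit, but it contradicts nothing in the document.

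The reply does not remove the mismatch. The abstract judges feasibility by a reduction and gives that reduction a power it does not have, and the pilot label does not turn a non-inferiority finding into evidence that failure falls. The mixed framing also reaches Sample size, which opens with a hypothesised decrease before turning to non-inferiority.

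**Conclusion.** The point holds as an inconsistency between the stated hypothesis and the planned test. The 80% in the abstract belongs to a one-sided 5% non-inferiority test with a 5-point margin, conditional on true failure rates of 22% and 15%. For the reduction the abstract describes, power at 129 per arm is about 30% two-sided or 42% one-sided under those same rates. These figures assume 129 analysed patients per arm and the usual large-sample tests; exact enumeration of the chi-squared test agrees closely, and Fisher's test is somewhat lower.

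The advance conclusion in the abstract's Discussion goes beyond what the planned test can show. The primary test, the number of patients and the data to be collected are unaffected; the stated power and the meaning given to a positive result need correcting.

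**What to change.** 1. **Abstract, Methods:** state that the primary hypothesis is non-inferiority of PSV + sigh for failure of assisted ventilation, with a margin of 5 percentage points at one-sided 5%, and that 129 per arm gives 80% power if the true rates are 22% and 15%.
2. **Background objective and main Discussion:** align with that wording. In the Discussion, say that the assumed fall from 22% to 15% enters the calculation as the expected benefit and is not itself the hypothesis tested with 80% power.
3. **Abstract, Discussion:** describe a positive result as failure not more than 5 points higher with sigh. Reserve any statement that sigh reduces failure for a significant superiority result.
4. **Optional:** if a claim of reduction is wanted, prespecify before database lock a superiority test of the same composite, run only if non-inferiority is met. Choose one sidedness and state its power (about 30% two-sided or 42% one-sided). Recruitment is under way and treatment is open-label, so the decision should be documented and dated.

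Items 1 to 3 cost wording and a less favourable stated power. Item 4 also adds a prespecified test. None needs extra patients.

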**Discussion:**

PROTECTION is a pilot randomized controlled trial testing the feasibility of adding sigh to PSV. If positive, it will provide physicians with an effective addition to standard PSV for lung protection, able to reduce failure of assisted ventilation. PROTECTION will provide the basis for a future larger trial aimed at verifying the impact of PSV + sigh on 28-day survival and ventilator-free days.

**Trial registration:**

ClinicalTrials.gov, NCT03201263. Registered on 28 June 2017.

**Electronic supplementary material:**

The online version of this article (10.1186/s13063-018-2828-8) contains supplementary material, which is available to authorized users.

## Background

Although mechanical ventilation is an effective support strategy for patients with acute hypoxic respiratory failure (AHRF), it has the potential to aggravate lung damage through the development of ventilation-induced lung injury (VILI) [1]. Ever since a landmark study demonstrated the association between the use of high tidal volumes during controlled mechanical ventilation and increased mortality [2], “protective” controlled ventilation with limited volume and pressure has become the recommended treatment for patients with AHRF, in order to minimize the risk of VILI [3]. Volutrauma and barotrauma (i.e., the key mechanisms causing VILI during controlled ventilation) might also occur during assisted ventilation, if excessive force generated by the respiratory muscles adds to the pressure delivered by the ventilator to determine high tidal volume and injurious transpulmonary pressure [4]. However, while protective strategies have been established for patients undergoing controlled mechanical ventilation (e.g., limiting plateau pressure to < 30 cmH_2_O), interventions that enhance lung protection during assisted ventilation are still lacking [5]. Around 30% of invasively ventilated patients with AHRF already breath spontaneously by day 1 after intubation [6] and early implementation of specific strategies to enhance lung protection during assisted ventilation may have a tremendous impact on clinical practice.

From a pathophysiological standpoint, during assisted ventilation, derecruitment and lung heterogenity may facilitate the generation of high regional barotrauma and volutrauma [7], thus increasing the risk of VILI [8–10]. The addition of cyclic short sustained inflations (sigh) to assisted ventilation is known to optimize recruitment and decrease heterogeneity in patients with AHRF [11–16]. Moreover, sigh might reduce the inspiratory effort and the tidal volume [11–16]. These physiologic studies generated the hypothesis that addition of sigh to pressure support ventilation (PSV, the most common assisted mechanical ventilation mode) might decrease the risk of VILI, potentially yielding faster weaning and improved clinical outcomes.

As prospective clinical trials including long-term use of sigh during assisted ventilation have not been performed yet, we conceived a pilot randomized controlled trial (RCT) to verify the clinical feasibility of the addition of sigh to PSV (PSV + sigh) in comparison to standard PSV. Therefore, the objective of the present trial is to determine whether ventilation by PSV + sigh can be applied early and safely in intubated patients with AHRF and successfully maintained until extubation. Specifically, the primary endpoint is to evaluate whether PSV + sigh, as compared to PSV, is associated with reduced failure of assisted ventilation, with failure defined as (1) prolonged switch to controlled ventilation; (2) use of rescue therapies for refractory hypoxia or (3) early need for reintubation after elective extubation.

## Methods

### Design

The PROTECTION (Pressure support ventilation + sigh in acute hypoxemic respiratory failure patients) trial is an investigator-initiated, international, multicenter, parallel randomized controlled two-arm trial that will be performed in intubated and ventilated patients with AHRF, who are admitted to the intensive care unit (ICU). The study will be conducted in adherence to the principles of the World Medical Association’s Declaration of Helsinki and in accordance with the Medical Research Involving Human Subjects Act (WMO). Ethics approval will be sought from each participating institution before starting enrollment and consent will be obtained for each patient following local regulations. The Institutional Review Board of the coordinating center approved the protcol on 12 June 2017 under reference number 318_2017bis. The trial was registered at www.clinicaltrials.gov with code NCT03201263 in June 2017. The Standard protocol items: recommendation for interventional trials (SPIRIT) checklist can be found in Additional file 1 and the SPIRIT figure is included in the main body of the manuscript (Fig. 1).

**Fig. 1 Fig1:**
[figure not shown]
Standard protocol items: recommendation for interventional trials (SPIRIT) figure. Schedule of enrolment, interventions, and assessments for the PROTECTION trial. PSV, pressure support ventilation

### Setting

The PROTECTION trial will be performed in the ICUs of 23 centers around the world (12 in Italy, 10 in other European countries, 1 in China). The coordinating center will be Policlinico Maggiore Hospital in Milan, Italy.

### Study population

Consecutive patients admitted with AHRF to each participating ICU, who have been intubated and switched to PSV between 1 and 7 days after intubation will be screened between 4 and 24 h from the start of PSV. Further inclusion criteria will be partial arterial pressure of oxygen (PaO_2_)/fraction of inspired oxygen (FiO_2_) ratio ≤ 300 mmHg (measured at clinical positive end-expiratory pressure (PEEP) and FiO_2_ values); clinical PEEP ≥ 5 cmH_2_O and stable Richmond Agitation-Sedation Scale (RASS) value of − 2 to 0. Exclusion criteria will be clinical PEEP ≥ 15 cmH_2_O; partial pressure of arterial carbon dioxide (PaCO_2_) > 60 mmHg; arterial pH < 7.30; PaO_2_/FiO_2_ ratio ≤ 100 mmHg (measured at clinical PEEP and FiO_2_ values); age < 18 years; presence of central nervous system or neuromuscular disorders; history of severe chronic obstructive pulmonary disease or fibrosis; AHRF fully explained by cardiac failure or fluid overload; evidence of active air leak from the lung (e.g., pneumothorax); cardiovascular instability (e.g., systolic blood pressure (SBP) < 90 mmHg despite vasopressors); clinical suspicion of elevated intracranial pressure; extracorporeal support; moribund status and refusal by the attending physician.

If an eligible patient is excluded from participation, the reason(s) for exclusion will be registered.

The Consolidated Standards of Reporting Trials (CONSORT) diagram of PROTECTION trial is presented in Fig. 2.

**Fig. 2 Fig2:**
[figure not shown]
The Consolidated Standards of Reporting Trials (CONSORT) diagram of the PROTECTION trial. PaO_2_, partial pressure of arterial oxygen; FiO_2_, fraction of inspired oxygen; PEEP, positive end-expiratory pressure; RASS, Richmond Agitation-Sedation Scale; PaCO_2_, partial pressure of arterial carbon dioxide; COPD, chronic obstructive pulmonary disease; PSV, pressure support ventilation

